### Power calculation

The sample size was calculated on the results from our migration study [13] and dietary intervention study [23] where we found a 0.56 (SD = 0.34) fall in CHD risk using the biomarker C-reactive protein for individuals on the substitution dietary intervention and no significant reduction in the other groups. Using a paired t-test, at 80% power, α<0.05, 25 subjects/arm will allow the detection of a 1 mmol difference in 2 hr glucose and 0.15 mmol change in NEFA suppression (this is ½ the difference seen between glucose tolerant and intolerant Indian Gujaratis in our migration study [14]).

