**Figure 1 F1:**
[figure not shown]
**Study Flow-chart**.

Each participant will be asked to attend three visits (screen, randomisation and follow-up). The screening visit will be used to initiate the consent process blood, and to assess inclusion criteria (eg dietary intake).

At randomisation and follow-up, blood pressure and anthropometry will be measured and an OGTT will be performed. Subjects will also be asked to complete a 4-day dietary record at randomisation and follow-up. The main metabolic measures will be 10 week changes in - OGTT metabolites and hormones (glucose, insulin, NEFA), adiponectin, leptin and lipids and lipoproteins (including serum triglycerides and HDL cholesterol).

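### The only effect and SD behind the sample size belong to C-reactive protein and need 6 or 7 subjects, not 25; the glucose and NEFA power has no SD and uses a paired test in a parallel trial

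*Protocol article*

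**What the plan says.** All of the sample-size reasoning is in the Power calculation section of the protocol article. It names two sources: "The sample size was calculated on the results from our migration study [13] and dietary intervention study [23". From these it reports one result with a measure of spread, without a unit or scale: "we found a 0.56 (SD = 0.34) fall in CHD risk using the biomarker C-reactive protein for individuals on the substitution dietary intervention". The result is for the substitution-diet group, and the other groups are said to show no significant reduction.

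The next sentence makes the power claim. "Using a paired t-test, at 80% power, α<0.05, 25 subjects/arm" "will allow the detection of a 1 mmol difference in 2 hr glucose", and likewise a "0.15 mmol change in NEFA suppression". A bracket gives the origin of the target: "this is ½ the difference seen between glucose tolerant and intolerant Indian Gujaratis in our migration study". No SD is given for glucose or for NEFA.

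Two other places bear on this. The Interventional trial section describes a parallel trial of 50 subjects in two arms, and the hypothesis under the objectives is a comparison of those arms. The main metabolic measures, given after Figure 1, are changes over 10 weeks in "OGTT metabolites and hormones (glucose, insulin, NEFA), adiponectin, leptin and lipids and lipoproteins (including serum triglycerides and HDL cholesterol". C-reactive protein is in neither that list nor the hypothesis. Glucose and NEFA (fatty acid) metabolism are in both.

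**The concern.** A reader who tries to rebuild the 25 per arm meets two obstacles.

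- The one effect that comes with an SD concerns a marker the article does not name as an outcome, and it is so large relative to its SD that it calls for far fewer subjects.
- The outcomes the size is meant to serve come with target differences but no variability. The test named for them answers a within-person question, whereas the trial asks a between-arm one.

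At stake is whether the randomised comparison has the stated 80% power. For the same SD of change, a two-sample test at 25 per arm has clearly less power than a paired test on 25 pairs, so the choice of test alone can decide whether the trial is adequately sized.

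**Working it through.** **Inputs (Power calculation section).** C-reactive protein fall 0.56, SD 0.34; targets 1 mmol (2-hour glucose) and 0.15 mmol (NEFA suppression); 25 per arm; power 80%; α 0.05. Sidedness is not stated. Two-sided is used below unless noted. Power is from the noncentral t distribution.

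**Formulas.** With Δ the difference and SD that of the change:
- paired: noncentrality = (Δ/SD)·√n, with n − 1 degrees of freedom
- two-sample: noncentrality = (Δ/SD)·√(n/2), with 2n − 2 degrees of freedom, n per arm

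**Step 1. Can 25 be reproduced from the printed effect and SD?** 0.56/0.34 = 1.647.

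| Test | Power just below | Smallest n reaching 80% |
|---|---|---|
| Paired t | n = 5: 0.784 | n = 6: 0.892 |
| Two-sample t | n = 6: 0.730 | n = 7 per arm: 0.807 |

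The normal approximation for two samples, 2(1.960 + 0.842)²/1.647² = 5.8, gives 6 per arm. At 25 per arm the power for this effect exceeds 99.9% under either t-test. Variants do not reach 25 either:
- one-sided: 5 pairs, or 6 per arm (two-sample t)
- SD multiplied by √2: 12 (normal) or 13 (t) per arm
- power 90% or 95%: 8 or 10 per arm (normal)

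Halving the effect to 0.28 does give 25 per arm in a two-sided two-sample t-test (24 by the normal approximation), but 14 pairs in the paired test that the article names.

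**Step 2. What must the SDs be for the glucose and NEFA claim to hold?** At n = 25 and 80% power the detectable standardised difference is 0.584 (paired) or 0.809 (two-sample).

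| Endpoint | SD required, paired | SD required, two-sample |
|---|---|---|
| 2-hour glucose, 1 mmol | 1/0.584 = 1.71 | 1/0.809 = 1.24 |
| NEFA suppression, 0.15 mmol | 0.15/0.584 = 0.257 | 0.15/0.809 = 0.185 |

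**Step 3. What does the paired test conceal?** Assume that the SD of change in each arm equals the value the paired test implies (1.71 or 0.257 mmol). The between-arm noncentrality is then 0.584 × √12.5 = 2.06, against a critical t of 2.01 on 48 degrees of freedom. Power is about 53%, and 80% needs 48 per arm.

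**Step 4. Range over the unknown glucose SD** (assumed values, difference 1 mmol, two-sample t):

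| SD of change (mmol) | Power at 25 per arm | n per arm for 80% |
|---|---|---|
| 1.0 | 93% | 17 |
| 1.25 | 79% | 26 |
| 1.5 | 64% | 37 |
| 2.0 | 41% | 64 |

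**The case against.** The strongest reply is that the section never says the C-reactive protein effect yields 25. It reports that effect as a result of previous research and then ties 25 per arm to glucose and NEFA, which are trial measures, with a target traced to the migration study. The missing SDs may be in the full protocol or the cited papers, since this is a condensed article.

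Much of that stands. A reader might infer that 25 per arm has no valid basis at all. The text does not support this: the migration study is also named as a source, and the glucose and NEFA claim can be neither reproduced nor refuted without SDs. A reader might also infer, from the match in Step 1, that 25 was obtained by halving the C-reactive protein effect. That is only a possible origin. The article attaches its one-half to the tolerant versus intolerant difference, and 25 follows equally well from the SDs in Step 2. Nor can one infer that C-reactive protein will go unmeasured. The list is of main measures and need not be exhaustive, and no objective depends on this marker.

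Two things survive. The article chose to present a derivation, and the one complete pair of inputs in it does not lead to its result. The paired t-test is something the article states, not something it omits, and it does not fit a comparison of two parallel arms.

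**Conclusion.** The concern holds as a fault in the stated justification. The printed effect and SD call for about 6 pairs or 7 per arm, against 25 stated, and they concern a marker outside the hypothesis and the listed measures. The 80% power for 2-hour glucose and NEFA suppression cannot be verified from the article and is stated for the wrong kind of test.

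The test mismatch is the more consequential part. The between-arm claim is correct only if the SDs of change are no larger than about 1.24 mmol (glucose) and 0.185 mmol (NEFA). If they are the 1.71 and 0.257 mmol that the paired test implies, power is about 53%. That figure is conditional: it rests on back-calculated SDs, a two-sided 5% test and complete data on 25 per arm. It does not show that the trial is underpowered, because the true SDs are not given.

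**What to change.** Rewrite the Power calculation section:

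1. Remove the C-reactive protein figures as a basis for the sample size.
2. For 2-hour glucose and NEFA suppression, state the SD of 10-week change and its source. If the earlier data give only a baseline SD, use SD of change = baseline SD × √(2(1 − r)) with an assumed correlation r between the two visits, shown over a range. This may be needed, since the article describes the migration study as an epidemiological comparison and mentions no repeat measurements.
3. Replace the paired t-test with a two-sample comparison of change, state whether it is two-sided, and give the power for 1 mmol and 0.15 mmol, or the detectable difference, at 25 per arm.

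No C-reactive protein assay is needed for this. The cost is one paragraph and a short calculation, with no change to procedures. The downside is that the stated power may become less favourable, or the detectable difference larger. With an SD of 1.71 mmol, for example, the detectable glucose difference is 0.809 × 1.71 = 1.38 mmol.

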### Objectives are as follows

(i) to establish the GI of existing (ie. produced in the UK) traditional, and regenerated (see (ii)) food staples of South Asian cuisine (specifically chapatti flour and basmati rice).

(ii) to develop will DHRMA test foods that have been specifically that are processed in a similar fashion to those available in rural India: basmati rice that is polished to a low level (less bran removed, grain quality distribution ratio score by KETT (Tokyo, Japan) of <35%)*, and stone-ground chapatti flour with added grains (oats, barley and chick pea).

(iii)to determine the efficacy of low GI DHRMA foods on indices of diabetes and CHD risk using a blinded, randomised controlled trial.

Note* KETT is an industry standard originating from Japan - a score based on the whiteness of rice. Generally amongst basmati rice sold in the UK, this score is around 40-44%.

The DHRMA study will focus on testing the hypothesis that a 10-week supply of DHRMA foods (reduced GI supply of chapatti stone ground, high protein wheat flour and high bran, unpolished white basmati rice) to healthy South Asians will result in favourable changes in cardio-metabolic risk factors (glucose tolerance, fatty acid, triglyceride and HDL cholesterol metabolism and central adiposity) as compared those randomised to commercially popular (market leaders) versions of chapatti flour and white basmati rice.

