### Interventional trial

This is a 10-week, blinded, parallel, randomised intervention trial in South Asians either DHRMA versions of stone ground chapatti flour and high bran white Basmati rice or the commercially popular white chapatti flour (Elephant atta, Premier Foods, UK) and white Basmati (Tilda, UK) will be supplied to participants.

The Inclusion criteria will include age <55 yrs, BMI <30 kg/m^2^, systolic/diastolic BP <140/90 mmHg (no antihypertensive use), South Asian ethnicity and use of chapatti flour or rice as part of their normal diet (>3 times a week) and >50% of energy derived from carbohydrates and <30% from fat - determined by 4-day food diaries, used previously [13]).

A total of 50 subjects will be randomised onto either arm in a blinded fashion, and supplied with study carbohydrates (see Figure 1). The study carbohydrates will be packaged by our industrial collaborator (East End Foods, UK), who randomise and allocate individual packet numbers to each test food (information relating to the contents will be stored with our collaborator and so blinded to study researchers and the study participants). The supply of rice and flour will be in clear, unlabelled 15 kg bags packaged within a white box with an assigned randomisation number and trial details. Random number allocation will be through a computer generated system, with no provision for factorisation.

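### The 80% power is stated for a paired t-test, which does not test the between-arm contrast that the trial is designed to answer

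*Protocol article*

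**What the plan says.** The Interventional trial section of the protocol article sets out the design: "This is a 10-week, blinded, parallel, randomised intervention trial in South Asians". It also gives the size: "A total of 50 subjects will be randomised onto either arm in a blinded fashion". Each participant receives one of the two food supplies.

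The hypothesis, at the end of the objectives, is that the DHRMA foods will improve cardio-metabolic risk factors "as compared those randomised to commercially popular (market leaders) versions of chapatti flour and white basmati rice". The text under the study flow-chart (Figure 1) gives the form of the outcome: "The main metabolic measures will be 10 week changes in" the glucose tolerance test, hormone and lipid measures. An oral glucose tolerance test is done at randomisation and again at follow-up.

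The Power calculation section then states: "Using a paired t-test, at 80% power, α<0.05, 25 subjects/arm will allow the detection of a 1 mmol difference in 2 hr glucose". The same sentence claims a detectable change of 0.15 mmol in NEFA suppression. The only SD in that section is 0.34, which belongs to a 0.56 fall in C-reactive protein from earlier work. No SD is given for 2-hour glucose or NEFA.

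**The concern.** The test named in the power statement does not match the comparison in the hypothesis. With one baseline and one follow-up assessment per person, the only pairing the article describes is each participant's own before and after. No matching of participants across arms is described. A paired test on an arm of 25 therefore asks whether that arm changed, not whether it changed more than the other arm.

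The two questions have different precision. If the SD of an individual's change is σ, the mean change in one arm has variance σ²/n, while the difference between two arms' mean changes has variance 2σ²/n. A sample size that just gives 80% for the first falls well short for the second at the same effect.

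This is the only justification given for the sample size. A reader who takes it at face value would expect the randomised comparison to have 80% power for 1 mmol of 2-hour glucose, and could misjudge how much a null result tells them.

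**Working it through.** **Inputs from the article:** 25 per arm, 50 in total; 80% power; α 0.05 (sidedness not stated; two-sided taken, one-sided also run); effects of 1 mmol (2-hour glucose) and 0.15 mmol (NEFA); paired t-test.

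**Assumptions:** the SD of change is equal in both arms, and the between-arm difference in change equals the stated effect.

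**1. Can the plan's 80% be reproduced?** Not independently, because neither SD is given. The C-reactive protein figures do not lead to 25 either: 2 × (1.960 + 0.842)² × (0.34/0.56)² ≈ 5.8, or 6 per arm. The statement therefore has to be solved backwards.

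**2. Solve the paired statement for its implied effect.** Paired t-test with n = 25, 24 degrees of freedom and noncentrality d√25 = 5d. Setting power to 0.80 at two-sided 0.05 gives d = 0.584. The implied SDs of change are:
- glucose: 1/0.584 = 1.71 mmol
- NEFA: 0.15/0.584 = 0.257 mmol

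**3. Put the same effect into the between-arm test.** Two-sample t-test of change, 25 per arm, 48 degrees of freedom, noncentrality d√(25/2) = 0.584 × 3.536 = 2.065. Power is 52.5%. Only d enters, so the result is the same for glucose and NEFA. Variants:
- two-sided normal approximation throughout: 50.8%
- one-sided t: 55.5%
- one-sided normal: 54.5%

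**4. Differences detectable between arms at 80%.** Two-sample t-test, 25 per arm, needs d = 0.809. With the implied SDs:
- glucose: 0.809 × 1.712 ≈ 1.38 mmol
- NEFA: 0.809 × 0.257 ≈ 0.21 mmol

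Both are about 38% larger than stated (0.809/0.584 = 1.385).

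**5. Baseline-adjusted follow-up instead of change scores.** With equal variances at both visits and baseline/follow-up correlation ρ, the residual variance is (1 + ρ)/2 times the variance of change. The effective d is then 0.584/√((1 + ρ)/2), with 47 degrees of freedom. The article gives no ρ, so a range is assumed:

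| ρ (assumed) | Power, 25 per arm |
|---|---|
| 0.3 | 71% |
| 0.5 | 65% |
| 0.7 | 59% |
| 0.9 | 55% |

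**6. If a two-sample test was in fact used.** The SD of change giving 80% at 25 per arm is 1/0.809 = 1.24 mmol for glucose and 0.15/0.809 = 0.185 mmol for NEFA. Unadjusted two-sample power for 1 mmol of glucose over assumed SDs of change:

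| SD of change (mmol, assumed) | Power, 25 per arm |
|---|---|
| 1.0 | 93% |
| 1.24 | 80% |
| 1.6 | 58% |
| 2.0 | 41% |
| 2.5 | 28% |

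**The case against.** The strongest reply is that paired may be a slip of wording for a two-sample calculation. The sentence mixes its terms: it counts subjects per arm and speaks of a difference in glucose, but of a change in NEFA. It also benchmarks the NEFA figure against a difference between two groups of people. On that reading 25 per arm does give 80%, provided the SDs of change are near 1.24 and 0.185 mmol. The article does not exclude those values. Equally, the preceding sentence describes a fall in one diet group and no significant reduction in the others, which fits a within-arm reading. The wording does not settle which calculation was run, so a reader might infer that the trial's power simply is 53%, and the article does not support that. What survives is that the power statement needs correcting on either reading: the test is wrong for the contrast, or the test is misnamed and the SD that would support it is absent.

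A second reply is that baseline adjustment would recover the power. It helps, but over the assumed correlations it reaches 55% to 71%, still below 80%.

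Two stronger readings are tempting and should be resisted. A reader might infer that efficacy will be judged by separate within-arm tests, calling the foods effective if one arm is significant and the other is not. The article names the paired test only for the power calculation and frames its hypothesis between arms; the analysis plan is not shown. A reader might also count the lack of a dropout allowance as part of the error. A condensed article commonly leaves that to the full protocol, and any loss rate used here would be invented.

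**Conclusion.** The power statement is wrong as written: it attaches 80% to a test that does not address the randomised comparison, and nothing else in the article repairs this. That conclusion rests on the text alone.

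The size is conditional. If the statement is literal (25 pairs, two-sided 0.05, equal SDs of change in both arms), an unadjusted between-arm comparison has about 53% power rather than 80%, a shortfall of about 27 percentage points. If a two-sample test was used and misnamed, the 80% could be right, but it cannot be checked without the SDs.

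**What to change.** Restate the power calculation for the between-arm difference in 10-week change, naming a two-sample test, the sidedness of α, the SD of change for 2-hour glucose and for NEFA, and the source of each SD. Report the power or detectable difference that 25 per arm delivers. Under the SDs implied by the present wording that would be about 1.38 mmol and 0.21 mmol for unadjusted change scores. If the intended analysis is baseline-adjusted follow-up, give it its own detectable difference with the assumed correlation; the 1.38 and 0.21 mmol figures do not carry over. If a two-sample test was used all along, correct the word paired and give the SDs.

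The cost is one recalculation and a few lines of text. No extra participants are needed; the price is a stated figure that may be less favourable.

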**Methods/Design:**

The Diabetes Health, Residence & Metabolism in Asians (DHRMA) study is a blinded, randomised, placebo controlled trial that analyses the efficacy of reduced glycaemic index (GI) staples of the South Asian diet, in relation to cardio-metabolic risk factors that are commonly perturbed amongst South Asian populations - primarily glucose, fatty acid and lipoprotein metabolism and central adiposity. Using a 10-week dietary intervention study, 50 healthy South Asians will be randomised to receive either a DHRMA (reduced GI) supply of chapatti (bread), stone ground, high protein wheat flour and white basmati rice (high bran, unpolished) or commercially available (leading brand) versions chapatti wheat flour and basmati rice. Volunteers will be asked to complete a 75g oral glucose tolerance test at baseline and at 10-weeks follow-up, where blood metabolites and hormones, blood pressure and anthropometry will also be assessed in a standardised manner.

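### The 80% power is tied to 25 per arm, which is also the number randomised, so as stated it assumes complete 10-week follow-up

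*Protocol article*

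**What the plan says.** Three statements in the protocol article bear on this point.

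- **Number randomised.** The Interventional trial section says "A total of 50 subjects will be randomised onto either arm in a blinded fashion". The Methods/Design paragraph of the abstract confirms that 50 is the total: "50 healthy South Asians will be randomised to receive either a DHRMA (reduced GI) supply". An equal split is not stated outright but is implied by the power statement.
- **Number in the power statement.** The Power calculation section reads "Using a paired t-test, at 80% power, α<0.05", and continues that "25 subjects/arm will allow the detection of a 1 mmol difference in 2 hr glucose and 0.15 mmol change in NEFA suppression".
- **Outcome.** The text after Figure 1 says "The main metabolic measures will be 10 week changes in - OGTT metabolites and hormones (glucose, insulin, NEFA" and other blood measures. An OGTT is done at the randomisation visit and again at the single follow-up visit.

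The text shown gives no expected loss rate, no inflation of the sample size and no replacement rule. It also gives no SD for the change in 2 hr glucose or NEFA. The only SD quoted, 0.34, belongs to C-reactive protein.

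**The concern.** A 10-week change is observed only in someone who has both OGTTs. With one post-baseline visit, a person who misses it has no later measurement to use in its place. The power statement needs a certain number of such people, and the design randomises exactly that number. Nothing is held in reserve for withdrawals or missed visits over 10 weeks of eating supplied staples at home.

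The 1 mmol and 0.15 mmol figures are the only detectable differences that the article gives for glucose and NEFA, so a null result is likely to be judged against them. If fewer than 25 per arm complete, the trial reaches 80% power only for somewhat larger differences than those stated.

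**Working it through.** **Inputs.** From the article: 50 randomised; 25 per arm; 80% power; alpha 0.05; "a 1 mmol difference in 2 hr glucose"; "0.15 mmol change in NEFA suppression". Assumed: two-sided test (sidedness is not stated), 1:1 allocation, and the loss rates.

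**Step 1: compare the two numbers.** 50 / 2 = 25 randomised per arm. The power statement also uses 25 per arm. The margin is 0.

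**Step 2: try to reproduce the 25.** This cannot be done forwards, because no glucose or NEFA SD is given. The C-reactive protein figures do not lead to 25: 0.56 / 0.34 = 1.65 SDs, for which about 6 pairs, or about 7 per arm unpaired, suffice. The stated 80% at 25 is therefore taken as given and the implied standardised effect d is solved from it.

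- Paired t-test: power = P(T > t[0.975, n−1]), where T is noncentral t with n−1 df and noncentrality d√n. Setting n = 25 and power = 0.80 gives d = 0.584. The implied SD of change is 1 / 0.584 = 1.71 mmol for glucose and 0.15 / 0.584 = 0.257 mmol for NEFA.
- Two-sample t-test: df = 2n−2 and noncentrality d√(n/2). Setting n = 25 per arm and power = 0.80 gives d = 0.809. The implied SDs are 1.24 and 0.186 mmol.

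**Step 3: hold d fixed and reduce the number with both OGTTs.**

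| Completers per arm | Assumed loss | Power, paired | Power, two-sample | Glucose difference at 80% (mmol; paired / two-sample) | NEFA difference at 80% (mmol, paired) |
|---|---|---|---|---|---|
| 25 | 0% | 80.0% | 80.0% | 1.00 / 1.00 | 0.150 |
| 24 | 4% | 78.2% | 78.3% | 1.02 / 1.02 | 0.153 |
| 22 | 12% | 74.3% | 74.6% | 1.07 / 1.07 | 0.161 |
| 20 | 20% | 69.8% | 70.3% | 1.13 / 1.12 | 0.170 |
| 18 | 28% | 64.7% | 65.4% | 1.20 / 1.19 | 0.180 |

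A one-sided alpha gives powers within about 2.5 points of these. The NEFA column assumes that NEFA, like glucose, sits at exactly 80% with 25 per arm.

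**Step 4: how likely is no loss at all?** If each person is lost independently with probability 5%, all 50 complete with probability 0.95^50 = 0.077. At 10% it is 0.90^50 = 0.005.

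**Step 5: do these figures carry over to the comparison between arms?** Only if the stated 80% was right for that comparison. Step 3 sets the SD separately for each test so that each gives 80% at 25. If the 80% really comes from the paired test, the SD of change is 1.71 mmol and d between arms is 1 / 1.71 = 0.584. The two-sample power is then about 53% at 25 per arm, 47% at 22 and 44% at 20. The difference detectable at 80% with 22 or 20 per arm is about 1.48 or 1.56 mmol. The figures in step 3 therefore show the relative cost of losses and are not values to print.

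**The case against.** The strongest objection is that the article says 25 per arm will allow detection. It does not say that 25 is the minimum or that it counts completers. Without an SD, slack cannot be ruled out. With a paired SD of change of 1.5 mmol (assumed), 25 pairs give 89% and 20 pairs still give 81%. One sample size also serves two endpoints, and both would sit at exactly 80% only if their standardised effects coincided, so at least one probably has some room. This stands, and it makes the result conditional. It does not remove the point, because 80% is the figure that the authors attach to 25.

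A second objection is that a journal article often leaves the allowance for attrition and the handling of missing follow-up to the full protocol, and that the flow-chart is not shown. That is fair as regards missing-data rules, and none is asked for here. But the article prints both numbers and they coincide. A fuller document could explain where slack lies; it could not turn 50 randomised into 25 complete pairs per arm after a loss.

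Third, the effect is small at first. One loss per arm takes 80.0% to 78.2% and 1.00 to 1.02 mmol. A reader might infer that any withdrawal breaks the power claim, or that 25 is exactly the number needed. The documents support neither reading.

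Fourth, it might seem that people who stop the study foods are not followed up. The text after Figure 1 asks each participant to attend all three visits, and nothing shown excuses those who stop. No change is needed there.

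**Conclusion.** The point holds in conditional form. The number randomised equals the number to which 80% power is attached, and the outcomes need both OGTTs, so the power as stated presumes complete follow-up. With assumed losses of 12% to 20%, power falls to about 70% to 75% and the detectable differences grow by about 7% to 13%. The result rests on accepting 80% at 25 per arm, a two-sided alpha of 0.05, equal arms and the assumed loss rates.

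This is a moderate overstatement in a figure that readers will rely on, and it does not show that the trial is unworkable. The use of a paired t-test to power a parallel-group trial is a separate question and may matter more. It bears on this point only because it decides which SD the restated figures should use.

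**What to change.** Keep 50 randomised and revise the Power calculation section as follows.

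1. Say that 25 per arm is the number randomised, and that the stated 1 mmol and 0.15 mmol differences require 25 per arm with both OGTTs.
2. Give the expected loss rate and the resulting number of completers per arm.
3. Restate the power, or the difference detectable at 80%, for that number. Give the SD of the 10-week change used for glucose and for NEFA, and compute the figure for the comparison between arms. Do not scale it from the paired t-test.

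The percentages in the working should not be copied into the text, because they inherit the unverified 80%.

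The change is to wording and one calculation, with no added participants or visits. The price is a less favourable stated figure: slightly so if the 80% already describes the comparison between arms, and more so if it came from the paired test.
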